We plan to conduct a cluster randomized controlled trial evaluating the efficacy of the aforementioned integrated mental health treatment and intimate partner violence prevention intervention as compared with a treatment as usual control group. In Nyarugusu Refugee Camp, the setting of this study, there are 7 zones within which refugees live. These zones are further subdivided into 52 villages. Women’s groups (described in further detail below; section IV. Participants) operate within these villages and will serve as the site of recruitment and the unit of randomization. Women entering the trial will be assessed for symptoms of mental health problems, intimate partner violence and other related constructs at baseline (week 1) and one post-intervention follow-up at week 10. All measurement and data collection is based on self-report indicators reported by the participant. The intervention is designed to last approximately 2 months (8 sessions, once per week for 8 weeks) with full participation in the study lasting 10 weeks (baseline to follow-up).

AIM 4: Conduct a qualitative process evaluation to examine facilitators and barriers to implementation of the research and intervention protocols.

We plan to conduct a qualitative process evaluation of the implementation of the Nguvu intervention and research protocols within the context of the randomized controlled trial described in Aim 3. To do so we will recruit a subset of participants (n=10), both high (n=5) and low attenders (n=5) from the intervention condition to participate in a qualitative interview with a member of the research team to discuss their experience participating in the intervention related to perceived challenges, risks, benefits, operations and acceptability. We will also qualitatively interview the 10 intervention facilitators and their clinical supervisor to identify their perspectives on successes and challenges of the intervention as well as their experiences as a provider of these services. Lastly, we will conduct qualitative interviews with seven representatives from partner agencies and the community advisory board to examine structural challenges to implementation as well as the perceived impact that implementing Nguvu had at the community and organizational level. We estimate that each of these interviews will take approximately one hour to complete and will be delivered by our trained research assistant team.

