1. Provide a sample size and a justification as to how you arrived at that number. If you use screening procedures to arrive at a final sample a table may be helpful.

Pilot Study:

We have chosen to include 60 women in the measurement validation and pilot intervention phase because this sample size will allow for each pair of facilitators (5 pairs in total) to run through the entire intervention starting with 12 women each. Sixty participants is also a sufficient sample size to meet the objectives of our measurement validation activities.

Randomized Controlled Trial:

Our primary outcomes are both assessed on a continuous scale, thus we conducted a sample size calculation for the randomized controlled trial intended for two-sample mean comparisons using one of our primary outcomes of interest, psychological distress. We gathered information from previous trials measuring our primary outcome(s) of interest in similar populations to estimate the following parameters used for the sample size calculation:

$$\sigma_{time1}^{2}=0.25$$

$$\sigma_{time2}^{2}=0.36$$

$$\rho=0.333$$

$$\sigma_{change}^{2}=0.55007$$

$$m=10$$

$$\mu_{1}=1.3$$

$$\mu_{2}=0.7$$

$$N=\frac{2\left( z_{\frac{\alpha}{2}}+z_{\beta} \right)^{2}(\sigma^{2})(1+\left( m-1 \right)\rho)}{{(\mu_{1}-\mu_{2})}^{2}}=\frac{2\left( 1.96+0.842 \right)^{2}(0.55007)(1+\left( 18.269-1 \right)0.333)}{{(1.3-0.7)}^{2}}=161.97$$

In order to have 80% power to detect a treatment effect of similar magnitude as previous trials that are roughly comparable in terms of intervention and population at the 0.05 significance level, we need 162 persons per group. To account for 10% attrition, we will recruit a target sample of 180 participants per group (360 total).

Process Evaluation:

We will conduct a total of 28 qualitative interviews as part of the process evaluation. We will recruit a subset of the participants that were enrolled in the randomized controlled trial (n=10) to participate in the process evaluation. We will recruit 10 intervention facilitators, their clinical supervisor (n=1) and 7 members of local partner organization to interview regarding implementation facilitators and challenges. These new participants will not be interviewed regarding personal health information and the focus of the interviews will be on program implementation.

Total Sample Size:

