**IV. Participants**

Describe the study participants and the population from which they will be drawn. Specify the inclusion and exclusion criteria. If you plan to include children, note their ages and whether you will include children in foster care. Note if the participants are particularly vulnerable in terms of cognitive limitations, education, legal migration status, incarceration, poverty, or some combination of factors.

Congolese refugee women residing in Nyarugusu camp in northwest Tanzania reporting a past-year history of intimate partner violence and experiencing moderate to severe psychological distress will be included in this study. We will initially invite women to participate that are members of women’s groups that operate throughout the camp. Women’s groups in Nyarugusu have been organized as a mechanism to strengthen social support among women in the camp. The types of women’s groups include cooking, weaving, tailoring and microfinance. Women’s groups are formed by IRC and other agencies in the camp; however, women from the community may propose to start a women’s group to these agencies as well. Each women’s group contains approximately 11-20 women and they each elect a leader that organizes group meetings and activities throughout the camp. Members organize most women’s group activities, however IRC and other agencies do occasionally provide skills trainings to women’s groups at the women empowerment center or other venues throughout the camp. In addition to recruitment through women’s groups, we will also include women that are referred to the program so long as they meet the following eligibility criteria:

1. Inclusion criteria:
   1. 18+ years of age
   2. Female
   3. Refugee from the DRC residing in Nyarugusu refugee camp
   4. Past-year history of intimate partner violence (survivor)
   5. Experiencing moderate to severe levels of psychological distress during the past month as measured by the 25-item Hopkins Symptom Checklist and the Harvard Trauma Questionnaire (Average Score >=1.75 on either checklist, indicating close to a moderate amount of distress)
2. Exclusion criteria:

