The primary goal of the study is to evaluate whether levels of psychological distress, intimate partner violence and/or functional impairment differ by exposure to the experimental intervention. To assess this quantitatively we will construct multilevel mixed effects models that account for the clustered design (within women’s groups) and allow for longitudinal analysis of the changes in these outcomes (while accounting for within-person clustering). Given that this is a randomized controlled trial, we do not anticipate any pre-treatment confounding, but will evaluate the similarity between groups in terms of important covariates at baseline. We are also including measures of hypothesized mediators and moderators of intervention efficacy that will be analyzed as our secondary analyses.

1. Describe whether you are collecting or storing personal identifiers, and if yes, why you need them, and when and how you plan to dispose of them. Signatures on consent forms are considered to be identifiers.

There are two points in the program at which we collect and store personal identifiers. The first is after the screening at which time we ask for the participant’s contact information to allow for communication with the participant throughout the follow-up period, as well as a signature (or thumbprint) on the consent forms. Immediately following the interview, this information will be placed in a double-lock safe in the research team office. The in-country project coordinator will input this information into a password-protected file that connects the participants alphanumeric ID with their name and contact information. This is the only place that this information will be connected. Afterwards, the physical contact sheet will be shredded. The consent forms will also contain personal identifiers. These consent forms will also be kept in the double-lock safe in the research team office.

6. Answer the following **if they are relevant to your study design**:

a. If the study has different arms, explain the process for assigning participants (intervention/control, case/control), including the sequence and timing of the assignment.

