The proposed study is cluster-randomized with women’s groups in the camp being defined as the clusters. Thus, randomization of women’s groups will occur before recruitment and data collection begin. The women’s groups in the camp will be randomized to intervention versus control by a faculty member in the Department of Mental Health at Johns Hopkins that has had no contact with the research field team (research assistants, in-country project coordinator). This independent faculty member will use a random allocation sequence generated by statistical software, which will remain with that independent JHSPH faculty member in Baltimore, not accessible to the research and intervention teams in Tanzania. All participants that are eligible and consent for enrollment will be asked to provide their address in the camp. Their study assignment will be determined by whether they reside in an intervention or control women’s group. The research assistants will be blind to study assignment. The in-country project coordinator, who does not conduct any data collection, will be responsible for coordinating communication with the intervention team to schedule sessions with enrolled participants belonging to intervention clusters. The process and timeline of conducting research study visits is the same between groups and will be managed by the research team.

- 1. If human biospecimens (blood, urine, saliva, etc.) will be collected, provide details about who will collect the specimen, the volume (ml) and frequency of collection, how the specimen will be used, stored, identified, and disposed of when the study is over. If specimens will be collected for use in future research (beyond this study), complete the Biospecimen Repository section below.

N/A

- 1. If genetic/genomic analyses are planned, address whether the data will be contributed to a GWAS or other large dataset. Address returning unanticipated incidental genetic findings to study participants.

N/A

- 1. If clinical or laboratory work will be performed at JHU/JHH, provide the JH Biosafety Registration Number.

N/A

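### No stratification, constraint or equal split of women's groups is described, yet randomisation alone is the ground for anticipating no pre-treatment confounding; with so few clusters, chance imbalance is a material possibility

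*Protocol*

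**What the plan says.** Section V.C.6.a (assignment to arms) makes women's groups the clusters and places their randomisation before recruitment and data collection. On the method it says: "This independent faculty member will use a random allocation sequence generated by statistical software". The sequence is held by a faculty member who has no contact with the field team. The section does not mention stratification, matching, blocking, constraint or an equal split of groups between arms, and the number of groups to be randomised is not stated.

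The brief data analysis plan in Section V.C says: "Given that this is a randomized controlled trial, we do not anticipate any pre-treatment confounding". The same sentence adds that the arms will be compared on important covariates at baseline, but does not say what follows if they differ. The planned analysis is a multilevel mixed model with women's group as a level and repeated measures within women.

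Group-level characteristics that could be known before allocation appear elsewhere. Section III (Aim 3) notes that "there are 7 zones within which refugees live". Section IV states: "The types of women’s groups include cooking, weaving, tailoring and microfinance". Section IV also gives group sizes of roughly 11 to 20 women.

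**The concern.** Randomisation balances covariates on average. How close a single allocation comes to balance depends on the number of units randomised and on how alike women within a unit are. A statement that no pre-treatment confounding is anticipated is reasonable for 360 independently randomised women. It is much less secure for a few dozen groups under the large within-group correlation that the sample-size calculation assumes.

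Two things are at stake. A visible baseline difference in a trial with about 10 to 18 clusters per arm leaves the result open to dispute, and a similarity check without a stated consequence invites adjustment chosen after seeing the data. Any precision available from group-level factors is also given up.

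Timing makes this more than a matter of detail. Groups are allocated before anyone is recruited. An analysis plan can add adjustment later, but no document written after allocation can restrict an allocation already made.

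**Working it through.** **Inputs (Section III, sample size).** Two-sided 5% level (z = 1.96), 80% power (z = 0.842), difference 1.3 − 0.7 = 0.6, variance of change 0.55007, baseline variance 0.25 (SD 0.5), ρ = 0.333. The cluster size m is 10 in the parameter list but 18.269 in the worked formula. The target is 162 per arm, or 180 after 10% attrition.

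**Reproducing the plan's figure.** The protocol says "at the 0.05 significance level, we need 162 persons per group".
- Before clustering: 2 × (1.96 + 0.842)² × 0.55007 / 0.6² = 23.99 per arm.
- m = 18.269: design effect 1 + 17.269 × 0.333 = 6.751, so N = 23.99 × 6.751 = 161.97. This reproduces, and 162 / 0.9 = 180.
- m = 10: design effect 1 + 9 × 0.333 = 3.997, so N = 95.9. This does not reproduce.

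**Implied number of groups.** 180 / 18.269 = 9.9 per arm, or 180 / 10 = 18 per arm.

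**Chance imbalance on one baseline covariate.** All 180 enrolled women per arm have a baseline value, so 180 is the relevant number. In baseline-SD units, the SD of the between-arm difference is √(2 × [1 + (m − 1) × ICC] / 180). The tail probability is 2 × [1 − Φ(0.25 / SD)].

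| ICC | m | Groups per arm | SD of difference | P(difference > 0.25 SD) |
|---|---|---|---|---|
| 0.333 | 18.269 | 9.9 | 0.274 | 0.36 |
| 0.333 | 10 | 18 | 0.211 | 0.24 |
| 0.10 (assumed) | 18.269 | 9.9 | 0.174 | 0.15 |
| 0.10 (assumed) | 10 | 18 | 0.145 | 0.09 |
| 0.05 (assumed) | 18.269 | 9.9 | 0.144 | 0.08 |
| 0.05 (assumed) | 10 | 18 | 0.127 | 0.05 |
| 0.333 | 5 (assumed) | 36 | 0.161 | 0.12 |
| individual randomisation | – | – | 0.105 | 0.02 |

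The first row in full: √(2 × 6.751 / 180) = 0.274; 0.25 / 0.274 = 0.913; P = 0.36.

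**Number of groups per arm.** If the sequence were a simple coin-flip, which the text does not exclude, the arms would differ by six or more groups with probability 0.26 (20 groups) or 0.41 (36 groups).

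**What restriction would gain.** A simulation kept the best 10% of 300 equal-split allocations on one group-level covariate whose correlation with the true group mean is r (ICC 0.333, 4,000 runs per scenario).

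| | Unrestricted | r = 0.3 | r = 0.5 | r = 0.8 |
|---|---|---|---|---|
| 20 groups of 18, P(> 0.25 SD) | about 0.36 | 0.34 | 0.29 | 0.16 |
| 36 groups of 10, P(> 0.25 SD) | about 0.24 | 0.22 | 0.19 | 0.08 |

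At r = 0 there is no gain.

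**Power at the substituted inputs (m = 18.269, 162 per arm).** Degrees of freedom are 2 × 162 / 18.269 − 2 = 15.7. The standard error is √(2 × 0.55007 × 6.751 / 162) = 0.214 and the noncentrality is 0.6 / 0.214 = 2.80, so power from the noncentral t is 75%. Now spend 3 degrees of freedom on strata (12.7 left) and let them explain a share of the between-group variance. The design effect becomes 0.667 + 18.269 × 0.333 × (1 − share).
- 0% explained: design effect 6.75, power about 73%.
- 10% explained (assumed): design effect 6.14, power 77%.
- 30% explained (assumed): design effect 4.93, power 86%.

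**The case against.** **Silence on restriction is not a choice against it.** A reader might infer that the sequence is unrestricted. The text does not say so; a blocked or stratified sequence is also generated by software. This stands. What can be said is that no restriction is described where the assignment process is set out.

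**The protocol does not simply rule out imbalance.** The sentence speaks of anticipation and goes on to a baseline comparison. This also stands, though the comparison comes after allocation and has no consequence attached.

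**The inputs are shaky.** The number of groups is not stated and m has two values. The single ρ of 0.333 also seems to produce the variance of change: 0.25 + 0.36 − 2 × 0.333 × 0.25 × 0.36 = 0.55006. It may therefore have been meant as a pre-post correlation. Not every group member will be eligible, so enrolled clusters may be smaller and more numerous. All this is fair, and it is why the range is shown. The protocol does, however, use 0.333 as the cluster correlation in its own design effect.

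**Chance imbalance is not bias.** A mixed model that handles clusters correctly carries this variation in its standard error and keeps its type I error. The longitudinal analysis also takes up at least part of a baseline difference in the outcome itself. This stands and limits the harm to precision and credibility. For the same reason, the raw SD of the difference (0.274 × 0.5 = 0.14 points at m = 18.269) should not be read as a 0.14-point error in a 0.6-point effect.

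**Restriction is neither free nor certain to help.** Nothing in the protocol shows that zone, activity or group size predicts distress or violence. If they do not, imbalance is unchanged and power falls slightly.

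**Conclusion.** The point holds in a limited form. The assignment section describes no restriction and no equal split of groups, and the analysis section treats randomisation as sufficient ground for anticipating no pre-treatment confounding. On the protocol's own inputs, the chance of a baseline difference above 0.25 SD on a given covariate is 24% to 36%, against about 2% under individual randomisation. This rests on reading 0.333 as the intracluster correlation of the baseline covariate and on about 10 to 18 groups per arm. It falls to 5% to 15% at an assumed correlation of 0.05 to 0.10, and lower still with more, smaller clusters.

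Two stronger readings are not supported. Sizeable imbalance cannot be called likely, because the probability is below one half in every scenario computed. Nor would restricted randomisation prevent it without cost: it reduces imbalance only as far as factors known beforehand predict group means. The consequence is a loss of precision and credibility, not a biased estimate. The change is still worth making because it is cheap and can only be made before groups are allocated.

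**What to change.** 1. In Section V.C.6.a, before allocation, state the number of groups and that equal numbers per arm are randomised within strata of zone (the seven zones pooled to three or four), or by covariate-constrained randomisation on zone, group type and group size. The same independent faculty member can run it.
2. In the data analysis plan in Section V.C, prespecify those factors and the baseline value of the outcome in the mixed model, so that adjustment does not depend on the similarity check.
3. Replace the sentence on pre-treatment confounding with one saying that chance imbalance is possible with few clusters and is handled by design and by prespecified adjustment.

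The cost is a listing of groups with zone, activity and size before allocation, a short allocation program, a few sentences, and about three degrees of freedom if zones are pooled to four strata. At the substituted inputs, power would go from 75% to about 73% if the factors explain nothing, and to 77% to 86% if they explain an assumed 10% to 30% of the between-group variance.
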